**Methods/Design:**

The trial is designed according to CONSORT Statement. It is a randomised, evaluator-blinded, match-pair group trial. Children with HCP will be randomised within pairs to either experimental or control group. The experimental group will perform an Action-Observation Therapy, called UP-CAT (Upper Limb-Children Action-Observation Training) in which they will watch video sequences showing goal-directed actions, chosen according to children UL functional level, combined with motor training with their hemiplegic UL. The control group will perform the same tailored actions after watching computer games. A careful revision of psychometric properties of UL outcome measures for children with hemiplegia was performed. Assisting Hand Assessment was chosen as primary measure and, based on its calculation power, a sample size of 12 matched pairs was established. Moreover, Melbourne and ABILHAND-Kids were included as secondary measures. The time line of assessments will be T0 (in the week preceding the onset of the treatment), T1 and T2 (in the week after the end of the treatment and 8 weeks later, respectively). A further assessment will be performed at T3 (24 weeks after T1), to evaluate the retention of effects. In a subgroup of children enrolled in both groups functional Magnetic Resonance Imaging, exploring the mirror system and sensory-motor function, will be performed at T0, T1 and T2.

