### Sample size

According to CONSORT guidelines [31,32] the sample size estimates were based on projected treatment effect on the primary outcome measure, the Assisting Hand Assessment (AHA). The AHA scale's responsiveness to change has been shown in a study in which Eliasson et al [38] used the scale as the outcome measure in evaluating the effects of a modified model of CIMT. The authors reported a significant effect size of 1.16. Calculation by a statistician indicated that in order to detect a 1.16 effect size at significant level of 0.05 and 80% power a minimum sample size of 12 per group is required in our study.

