### Randomisation

After enrolment, children will be block randomised into pairs according to their activity level at House Functional Classification System [36,37] (grade 6-8 vs 4 or 5) using a computer generated set of random numbers. A computer random allocation will also be used to randomly assign the subjects of each pair to experimental or control group by a computer random allocation. We choose a matched pairs design because it minimises the likelihood of group differences at baseline that has often been present in UL rehabilitation studies [39]. All randomisation, sequence generation, and preparation of group allocation materials will be performed by a third party, who has no direct contact with the clinical aspects of the trial. The master list of random numbers will be located in locked cabinets only accessible at completion of the RCT for analysis.

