### Analyses

Clinical Data will be managed and analysed using the Statistical Package for Social Sciences (SPSS version 16.0). Descriptive statistics (means, standard deviation) will be calculated to summarise the data set for both groups and to identify potential baseline differences between the groups; p values will be used to indicate the strength of the evidence, a significant level of 0.05 will be used. Initially between group differences will be evaluated at baseline (T0) assessment point using Mann-Whitney U independent sample test for all Outcome Measure chosen. Within group changes between baseline and follow-up assessment (T1 and T2) will be evaluated using Wilcoxon matched-pairs sign rank test. A second level analysis with independent sample t test of the differences between the follow-up assessment and baseline (T1 vs T0 and T2 vs T0) will be performed for the comparison of the rehabilitative gain between the two groups. Moreover, Cohen's d values and their 95% confidence interval will be calculated to obtain a pre-post intervention effect size [70]. According to Cohen's work values of effect size below 0.2 will be considered to reflect "no effect", values from 0.2 to 0.5 a "small effect", values between 0.5 and 0.8 a "medium-sized effect", and values > 0.8 "large effect".

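### The arms are compared by an unadjusted t test on change, which over-corrects for baseline; an analysis adjusted for the T0 score would be safer, and more precise unless the pre-post correlation is about 0.9 or higher

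*Protocol article*

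**What the plan says.** The Analyses section sets out three steps for the clinical outcomes. It starts with a baseline comparison: "Initially between group differences will be evaluated at baseline (T0) assessment point using Mann-Whitney U independent sample test for all Outcome Measure chosen". Within-group change is then tested by the Wilcoxon signed-rank test. Last comes the only comparison between arms, an independent-samples t test on follow-up minus baseline: "T1 vs T0 and T2 vs T0) will be performed for the comparison of the rehabilitative gain between the two groups". No covariate is named, and the section does not say what follows from a baseline difference.

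The Randomisation section pairs children on House grade (6-8 against 4 or 5) and randomises within pairs, because "it minimises the likelihood of group differences at baseline that has often been present in UL rehabilitation studies". The Sample size section gives the scale of the trial: "a minimum sample size of 12 per group is required in our study".

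**The concern.** Every child has a T0 score, but the between-arm test uses it only by subtraction. A change score removes the whole of a baseline difference, although only the fraction rho of it is expected to persist to follow-up. The arm that starts lower by chance therefore tends to show the larger gain, whatever the treatment does. With 12 per arm such differences are common, and the Randomisation section itself names baseline imbalance as a recurring problem in this field.

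The baseline significance test does not guard against this. Allocation is random, so its null hypothesis is true by design. At this sample size it would also miss most imbalances large enough to matter. At stake are how far the single efficacy comparison depends on the luck of the draw and, if rho is moderate, some power.

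**Working it through.** **Inputs.** From the Sample size section: effect size 1.16, 5% level, 80% power, 12 per group. From the AHA section: smallest detectable difference 3.65 raw points (0.76 logits). Assumed: a two-sided test, since sidedness is not stated, and rho from 0.5 to 0.95, since no figure is given. The effect of 1.16 is taken on the SD of change.

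**The plan's own figure.** n per group = 2 × (1.96 + 0.84)² / 1.16² = 11.7, so 12. The stated size reproduces. By the noncentral t distribution on 22 degrees of freedom, 12 per group gives 77.5% power. This holds for the change-score test at every rho.

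**Precision.** Let s² be the outcome variance, equal at both times.

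- Change score: variance proportional to 2(1 − rho)s².
- ANCOVA: variance proportional to (1 − rho²)s².
- Large-sample ratio: (1 + rho)/2.
- Estimating the slope with N = 24 multiplies this by about 1 + 1/20 = 1.05.

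ANCOVA power uses 21 degrees of freedom and effect 1.16/√ratio.

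| rho | (1 + rho)/2 | × 1.05 | ANCOVA power | Change-score power |
|---|---|---|---|---|
| 0.5 | 0.75 | 0.79 | 86.3% | 77.5% |
| 0.7 | 0.85 | 0.89 | 81.8% | 77.5% |
| 0.8 | 0.90 | 0.95 | 79.6% | 77.5% |
| 0.9 | 0.95 | 1.00 | 77.4% | 77.5% |
| 0.95 | 0.975 | 1.02 | 76.4% | 77.5% |

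Break-even is where 1.05(1 + rho)/2 = 1, that is rho = 2/1.05 − 1 = 0.905. Simulation (20,000 trials per rho) gave ANCOVA power of 86.3%, 81.9%, 79.6%, 77.7% and 76.1%. Both tests kept about 5% type I error.

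**Dependence on imbalance.** Ignoring matching, the baseline difference has standard error √(2/12) = 0.41 SD, and its chance of exceeding 0.5 SD in either direction is 22%. The change score over-corrects by (1 − rho) SD per SD of imbalance. In units of the SD of change, a one-standard-error imbalance shifts the estimate by 0.41 × (1 − rho)/√(2(1 − rho)) = 0.41 × √((1 − rho)/2):

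- rho 0.7: 0.41 × 0.387 = 0.16
- rho 0.8: 0.41 × 0.316 = 0.13
- rho 0.9: 0.41 × 0.224 = 0.09

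The factor √((1 − rho)/2), with a minus sign, is also the correlation between the estimate and the baseline difference: −0.39 at rho 0.7 and −0.22 at 0.9. At rho 0.7, by normal approximation, the nominal 2.5% chance of a false result favouring the worse-starting arm becomes P(Z > (1.96 − 0.387)/√(1 − 0.15)) = P(Z > 1.71) = 4.4%, given a one-standard-error imbalance.

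**The T0 test.** Power to flag a 0.5 SD difference with 12 per arm is about 22%. This is a t-test figure used as an approximation for the Mann-Whitney test.

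**What the article implies about rho.** The smallest detectable difference gives a standard error of measurement of 3.65/(1.96√2) = 1.32 raw points. From measurement error alone, rho = 1 − 1.32²/SD², which falls below 0.9 only if the between-child SD is under 1.32/√0.1 = 4.2 points (0.87 logits). Variation in response between children would lower rho further, but no figure is given for it.

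**The case against.** The planned test is a legitimate one. It is unbiased over randomisations, it holds its type I error, and gain from baseline is a natural quantity in rehabilitation. The conditional shift of 0.09 to 0.16 SD of change is well under half of the estimate's own standard error (0.41 SD of change) and small beside the design effect of 1.16. Within-pair randomisation on House grade, which probably correlates with AHA, should make imbalance smaller than 0.41 SD suggests. The high reliability reported for the AHA points to a high rho, where adjustment gains little. All of this stands, and it limits the point to an improvement in method.

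A reader might infer three stronger things that the article does not support:

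- **That chance imbalance is left uncorrected.** Subtraction does correct for baseline; it corrects too much.
- **That precision is certainly lost.** This depends on a rho that the article does not give. The large-sample ratio would suggest a 5 to 15% saving at rho 0.9 to 0.7, but the cost of estimating the slope reduces this to about 0 to 11%.
- **That a baseline difference would go unhandled.** The article is silent on this, and the full plan may deal with it.

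The objection does not remove the dependence on baseline. House grade has only two levels in the pairing, while the AHA raw score runs from 22 to 88, so children within one level can still differ. Nor is a high rho assured: eligibility is limited to House grades 4 to 8, and for ABILHAND-Kids the reported reproducibility of 0.91 is already near break-even before any variation in response.

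**Conclusion.** The point holds as a recommended improvement to a valid analysis. The change-score estimate stays correlated with whatever baseline imbalance occurs, and the T0 significance tests neither detect nor repair that. The shift is at most about 0.16, 0.13 and 0.09 SD of change at rho 0.7, 0.8 and 0.9 for a one-standard-error imbalance; matching will reduce it by an amount the article does not allow one to calculate. Adjustment gains about 9, 4 and 2 points of power at rho 0.5, 0.7 and 0.8, nothing near 0.9, and loses about one point at 0.95. These figures rest on an assumed rho, equal variances at both times, a linear relation to baseline, and 24 children with complete data.

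**What to change.** In the Analyses section, prespecify the between-arm comparison of AHA at each follow-up as an ANCOVA with arm, the T0 value of AHA and House stratum (6-8 against 4 or 5). Do the same for MUUL and ABILHAND-Kids, each with its own T0 value. Replace the Mann-Whitney tests at T0 with a descriptive baseline table by arm.

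The cost is wording and two residual degrees of freedom (22 to 20), with no new data. The powers tabulated above adjust for T0 only. If House stratum is balanced between arms and explains nothing beyond T0, the ratio at rho 0.95 becomes 0.975 × (1 + 1/19) = 1.026. Power on 20 degrees of freedom is then 76.1% instead of 76.4%, so the price at a very high rho stays at about one point.

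### Any Cohen's d below 0.2 is labelled as no effect from the point estimate alone and with no lower bound, which 12 children per group cannot support

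*Protocol article*

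**What the plan says.** In the Analyses section, the two groups' gains are compared by an "independent sample t test of the differences between the follow-up assessment and baseline (T1 vs T0 and T2 vs T0"), at the 0.05 level. The section then adds an effect size: "Cohen's d values and their 95% confidence interval will be calculated". This d is described as a pre-post measure; neither its standardiser nor a pre-post correlation is given.

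The bands follow. The lowest reads "values of effect size below 0.2 will be considered to reflect 'no effect"; from 0.2 to 0.5 is small, 0.5 to 0.8 medium, and above 0.8 large. Neither the sign of d nor its absolute value is mentioned, and nothing says how the interval bears on the label.

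The Sample size section takes an effect size of 1.16, a 0.05 level and 80% power as its inputs and concludes: "a minimum sample size of 12 per group is required in our study". The abstract gives the same total as pairs: "a sample size of 12 matched pairs was established".

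**The concern.** Of the four labels, only the lowest asserts a negative finding about the treatment. A point estimate below 0.2 supports that assertion only if the estimate is precise enough to rule out effects that matter. A trial sized for an effect of 1.16 need not have that precision, so the label may describe lack of information as absence of effect.

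The second problem is in the wording. Every negative number is below 0.2, so a decline from baseline, or a difference favouring control, falls into the same band as a trivial gain.

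At stake is the description of the result in what the article presents as the first trial of this therapy in childhood. A reader who takes the adjective at face value could believe that the therapy had been shown not to work, or could miss a deterioration.

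**Working it through.** **Inputs.** From the Sample size section: effect size 1.16, alpha 0.05, power 80%, 12 per group. From the Analyses section: band limits 0.2, 0.5 and 0.8. Assumed: normal data, two-sided alpha (the sidedness is not stated), and, for raw-SD standardisation, a pre-post correlation r from 0 to 0.95.

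**1. The plan's own figure.** n per group = 2(1.96 + 0.842)² / 1.16² = 15.70 / 1.346 = 11.7, rounded up to 12. The stated size reproduces under the two-sided normal approximation.

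**2. 95% intervals at d = 0.19, just inside the lowest band.** Intervals for the first two forms of d come from inverting the noncentral t: find the two noncentrality values at which the observed t cuts off 2.5% in each tail, then divide by the same root that turned d into t.

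- Paired d, standardised by the SD of change: t = 0.19 × √12 = 0.658, 11 df. Interval -0.39 to 0.76. Medium is included; large (above 0.8) is narrowly excluded.
- Between-arm d: t = 0.19 × √(12/2) = 0.465, 22 df. Interval -0.61 to 0.99. Medium and large are both included.
- Pre-post d, standardised by the raw SD: SE = √[2(1 - r)/12 + d²/(2 × 11)], limits d ± 1.96 SE. For r = 0.8: SE = √(0.0333 + 0.0016) = 0.187, upper limit 0.19 + 1.96 × 0.187 = 0.56.

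| r (assumed) | Interval at d = 0.19, raw SD |
|---|---|
| 0 | -0.61 to 0.99 |
| 0.5 | -0.38 to 0.76 |
| 0.8 | -0.18 to 0.56 |
| 0.9 | -0.08 to 0.46 |
| 0.95 | -0.01 to 0.39 |

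Medium is therefore included up to r = 0.8 and excluded from r = 0.9.

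**3. How often a true medium effect (d = 0.5) gets the lowest label.** P(observed d < 0.2):

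- between arms, noncentral t with 22 df and noncentrality 0.5√6: 23%;
- paired, SD of change, 11 df and noncentrality 0.5√12: 15%;
- pre-post, raw SD, by simulation: 15% at r = 0.5, 5% at r = 0.8, 1.2% at r = 0.9.

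**4. The missing floor.** Take a paired d of -0.8: t = -0.8 × √12 = -2.77 on 11 df, interval -1.44 to -0.13, wholly below zero. Since -0.8 < 0.2, the literal rule gives it the lowest label. The between-arm interval at the same value, -1.63 to 0.04, just includes zero.

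**The case against.** The strongest reply is that the bands decide nothing. The groups are compared by the t test; d comes afterwards as a supplement with conventional labels, and no success, failure or stopping decision is attached to a band. This stands, and it limits the weight of the point. A reader might infer that the plan contains a rule for declaring the therapy ineffective; the article contains no such rule.

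A second reply is that each d comes with a 95% interval, so the imprecision would be visible. This stands in part. The interval would be printed, but the label is defined without it, and an interval reaching 0.76 beside a label denying any effect gives the reader two incompatible messages.

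Third, the article calls this d a pre-post measure. It is tempting to say that 12 per group cannot separate 0.2 from a large effect. That holds between arms, but not for a paired d standardised by the SD of change, where the upper limit even at 0.20 is 0.77. It is also tempting to set the label against the 0.05 test, because a between-arm d must reach 0.847 for significance and every significant benefit would then be called large. That concerns a d the article does not describe; for a paired d the critical value is 0.635, inside the medium band. Effect size and significance also answer different questions.

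Last, such bands are ordinarily read on magnitude, and a condensed article may simply have left that out. A negative d would also keep its sign in the reported value. Both points are fair, so the claim that a decline would go unreported is not supported; what remains is that the literal wording mislabels it.

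**Conclusion.** The point holds as a modest correction to interpretation. With 12 children per group, a d just under 0.2 does not support the conclusion that there is no effect. It is compatible with a medium effect for a paired d standardised by the SD of change, and with a large one between arms. For a pre-post d the chance that a true 0.5 receives the lowest label is not one figure: it runs from about 1% to 15% over the standardisers and correlations examined (raw SD with r from 0.5 to 0.9, and the SD of change). With raw-SD standardisation and r of 0.9 or more, the imprecision argument no longer reaches medium effects. The missing lower bound depends on none of these assumptions.

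No change in sample size follows. Nor should the label be reserved for intervals lying wholly within ±0.2: that is an equivalence criterion, which between arms needs about 200 per group even at d = 0 (half-width 1.96 × √(2/200) = 0.196), and the article sets no equivalence aim.

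**What to change.** Amend the banding text in the Analyses section so that:

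- the bands apply to the absolute value of d, with the sign reported and a negative value described as worsening (or as favouring control, if d is between arms);
- the lowest band is called a negligible observed effect;
- each label is read with the 95% interval already planned, and the result is called inconclusive when that interval also includes medium or larger effects.

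Naming the standardiser of d in the same place would settle which interval applies.

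The cost is a sentence or two, with no new data and no change to the t test. The downside is that a trial of this size will seldom be able to claim absence of effect: for a paired d standardised by the SD of change, even an observed value of 0 has an interval of -0.57 to 0.57 and would be inconclusive. That reflects what 12 children per group can show.

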## Discussion

The paper presents the background and the design for a matched pairs randomised trial for evaluating the efficacy of action-observation therapy in improving UL activity in children with HCP. The study is the first to provide this new type of treatment in childhood. Furthermore, it is based on rigorous scientific designing, according to CONSORT guideline [33,34], as recommended by the evidence-based medicine. Finally, the set of exercises designed for the trial are child-oriented and tailored according to the grade of UL impairment.

## List of abbreviations

HCP: Hemiplegic Cerebral Palsy; CP: Cerebral Palsy; UL: Upper Limb; UP-CAT: Upper Limb Children Action-Observation Training; RCT: Randomised controlled trial; CONSORT: Consolidated Standards of Reporting Trials; BoNT-A: Botulinum toxin A; CIMT: constraint-induced movement therapy; HABIT: hand-arm bimanual intensive training; MNs: mirror neurons; MS: Mirror neuron System; PET: Positron Emission Tomography; MRI: Magnetic Resonance Imaging; fMRI: functional Magnetic Resonance Imaging; TMS: Trancranial Magnetic Stimulation; IPL: Inferior Parietal Lobule; PMv: ventral Pre-Motor cortex; IFG: Inferior Frontal Gyrus; MEPs: Motor Evoked Potentials; M1: primary motor cortex; DLPFC: dorsolateral prefrontal cortex; OTI: Observation To Imitate; MAS: Modified Ashworth Scale; AHA: Assisting Hand Assessment; ICC: Intraclass Correlation Coefficient; MUUL: Melbourne Assessment of Unilateral Upper Limb Function; SDD: Smallest Detectable Difference; ICF: International Classification of Functioning, Disability and Health; AIP: anterior intraparietal area; ROI: Region-Of-Interest; SR: Simple task Right hand; SL: Simple task Left hand; CR: Complex task Right hand; CL: Complex task Left hand; BOLD: Blood oxygen level dependent; EPI: Echo Planar Imaging; GLM: General Linear Model; SPSS: Statistical Package for Social Sciences.
